### Add-on placenta biomarker and CTG study

The development of improved surveillance tools to detect intrapartum or antepartum fetal stress is needed to prevent neonatal adverse outcomes, as CTG has limitations. We have previously found that predelivery circulating maternal antiangiogenic protein concentrations, produced by the placenta, may improve automated alerts produced by the Oxford System for computerized intrapartum monitoring (OxSys) 1.7 prototype (32). Depending on the technical feasibility, a predelivery placenta-associated biomarker and computerized antepartum and intrapartum fetal heart rate pattern study is planned in collaboration with UK researchers using data from the women in the HOME study.

### Sample size

The sample size calculation is based on the non-inferiority design and will be calculated for the primary clinical composite outcome (described above and in Table 2). The non-inferiority margin was set to 10% (i.e., a difference larger than 10% will be considered clinically significant), based on careful clinical considerations. The expected proportion of the outcome was set to 10%, based on the rate of the primary composite outcome observed in the first 80 women recruited to the hospital-monitored group in the HOME study. If there is no true difference between the home-monitored and the hospital-monitored groups' primary composite outcomes (10% in both groups), a total of 224 women with high-risk pregnancies (112 women in each group) is required. With this number of participants, we have a power of 0.80, ensuring that the upper limit of a one-sided 95% confidence interval will exclude a difference in favor of the hospital-monitored group of more than 10%. An additional six women will be invited to take potential dropouts into account. Further, due to the non-parallel group design (women were not randomized to either group, but are first mainly allocated to the hospital-monitored group and then to the home monitored group, pending on availability of home monitoring resources and equipment), another 20 women will be recruited to adjust for potential confounding factors such as parity and gestational age (totalling 250; 125 women in each group).

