**Discussion:**

The implementation of a home care service for women with high-risk pregnancies requiring intensified surveillance is expected to be equally safe and more comfortable and convenient for the women, with lower economic costs.

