Recent technological development has generated new opportunities for health surveillance outside the hospital, i.e., at home. Home monitoring systems for high-risk pregnancies, with the opportunity for patient registration of CTG, have not been tested or established in most countries, including Norway. After the planning of the home monitoring of high-risk pregnancies (HOME) study, two articles reporting on outcomes after home monitoring of high-risk pregnancies have been published: one retrospective study of 8 years of practice in Denmark (5) and one randomized controlled trial from the Netherlands (6). Both concluded that home monitoring may be a safe alternative to inpatient hospital care for selected women with high-risk pregnancies. Home monitoring of blood pressure in pregnancy poses challenges, as blood pressure can rise rapidly during pregnancy. Monitoring of blood pressure at home in pregnant women with gestational hypertension has, however, demonstrated better compliance with guidelines, likely lowering the burden on public health resources (7).

Any change in clinical practice needs to be thoroughly evaluated, including an evaluation of clinical outcomes. Thus, in this study, clinical safety, patient-reported outcomes, and healthcare economics following the introduction of home monitoring in high-risk pregnancies will be investigated. Ultimately, personalized follow-up with more telemonitoring opportunities and flexibility may enable the much in-demand specialist resources at obstetric departments (e.g., midwives and obstetricians) to focus on the patients with the greatest need for in-hospital follow-up.

The hypothesis in this clinical study is that home monitoring in selected high-risk pregnancies does not increase the risk of severe adverse maternal or fetal outcomes for women and their fetuses compared to similar pregnancies being followed up through hospitalizations and/or frequent outpatient visits. We also anticipate increased patient-reported satisfaction in line with positive patient expectations from general technology-enabled care solutions (8) and findings from our own preclinical expectation study related to the HOME study (9). Finally, we expect that the freeing up of hospital beds will reduce hospital costs and thereby result in a positive health economic assessment, despite the increased device costs and reorganization of the hospital’s follow-up system.

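### The 10-point non-inferiority margin equals the whole expected rate of a death and severe-morbidity composite, so meeting it excludes a doubling but does not show that risk is not increased

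*Protocol article*

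**What the plan says.** The Sample size section of the protocol article fixes every element of the rule.

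- Margin: "The non-inferiority margin was set to 10% (i.e., a difference larger than 10% will be considered clinically significant), based on careful clinical considerations".
- Base rate: "The expected proportion of the outcome was set to 10%, based on the rate of the primary composite outcome observed in the first 80 women", all of them under hospital monitoring.
- Power: 0.80 when both groups have a true rate of 10%, with 112 women per group, raised to 125 per group for dropout and confounder adjustment.
- Decision rule: the design is described as "ensuring that the upper limit of a one-sided 95% confidence interval will exclude a difference in favor of the hospital-monitored group of more than 10" percent.

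Table 2 defines the composite as direct maternal death, severe maternal morbidity or organ damage (among others sepsis, eclampsia, cerebral hemorrhage, HELLP and DIC), and fetal or neonatal death.

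The Introduction states the hypothesis that "home monitoring in selected high-risk pregnancies does not increase the risk of severe adverse maternal or fetal outcomes". The Data analysis section plans logistic regression with parity and gestational age as covariates, reported as odds ratios with 95% confidence intervals plus crude proportions. It does not list a risk difference, although the margin is set on that scale.

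**The concern.** The margin and the expected rate are the same number. At the assumed rate, the home-monitored group's risk has to reach 20%, against 10% in hospital, before it sits at the margin. That is 10 additional severe events per 100 women, a risk ratio of 2.0 and an odds ratio of 2.25.

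A pass is likely to be read against the stated hypothesis, that is, as evidence of no increase in severe outcomes. The rule cannot carry that reading, because it is often met when a real increase of 3 to 5 points exists. The Discussion says the results may affect monitoring practice, so the gap between what is shown and what is claimed matters.

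The margin is also fixed in absolute terms while the base rate comes from only 80 women. Its relative meaning will move with the rate finally observed.

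**Working it through.** **Inputs from the Sample size section.** Expected rate 0.10 in both groups, margin 0.10, one-sided 95% limit, power 0.80, 112 per group required, 125 per group planned.

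**Step 1: reproduce the stated sample size.** With the unpooled normal approximation,

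n per group = (z₀.₉₅ + z₀.₈₀)² × [p(1−p) + p(1−p)] / margin² = (1.645 + 0.842)² × (2 × 0.10 × 0.90) / 0.10² = 6.185 × 0.18 / 0.01 = 111.3, rounded up to 112, or 224 in total.

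This matches the protocol. One-sided 0.025 would give 142 per group. The stated figure therefore confirms an absolute 10-point margin and a one-sided 0.05 level.

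**Step 2: how often the rule is met.** The rule passes when

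(p_home − p_hosp) + 1.645 × √[p_home(1−p_home)/n + p_hosp(1−p_hosp)/n] < 0.10,

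using observed proportions. Its probability is the sum of the product of the two binomial probabilities over all pairs of event counts that pass, with n = 125 per group. The Newcombe limit is a check that the type of interval does not drive the result.

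| True hospital rate | True home rate | Risk ratio | Passes (Wald) | Passes (Newcombe) |
|---|---|---|---|---|
| 10% | 10% | 1.0 | 85% | 82% |
| 10% | 13% | 1.3 | 55% | 53% |
| 10% | 15% | 1.5 | 34% | 32% |
| 10% | 20% | 2.0 | 5.5% | 5% |
| 5% | 5% | 1.0 | 97% | 96% |
| 5% | 10% | 2.0 | 47% | 41% |
| 5% | 15% | 3.0 | 6% | 5% |
| 18.8% | 18.8% | 1.0 | 65% | 65% |

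With 112 per group (Wald, hospital rate 10%) the figures are 50% at a home rate of 13%, 31% at 15% and 5% at 20%.

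**Step 3: an observed result that passes.** Take 16 home events against 12 hospital events, 125 per group: 12.8% against 9.6%, a difference of 3.2 points and a risk ratio of 1.33. The standard error is √(0.128 × 0.872/125 + 0.096 × 0.904/125) = 0.0398. The upper limit is 0.032 + 1.645 × 0.0398 = 0.0975, just under 0.10, so the result passes.

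**Step 4: uncertainty in the base rate.** The article gives no event count. If 10% of 80 women means 8 events (an assumption), the exact 95% interval is 4.4% to 18.8%. At 5%, the margin corresponds to a risk ratio of (5 + 10)/5 = 3.0. At 18.8%, the margin is 10/18.8 = 53% of the base rate. The 5% and 18.8% rows of the table show what this does to the rule in each direction.

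**The case against.** **The margin is disclosed and is a clinical judgement.** The article says openly what the margin is and that it rests on clinical considerations, and a condensed article may leave the fuller rationale to the complete protocol. This stands. The point here is not that a rationale is missing or that another margin is right. No rationale would alter the probabilities above or what a pass excludes.

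**Every non-inferiority rule often passes true differences inside its margin.** This also stands, and at the margin the rule behaves as designed. It has force here only because the interior of the margin covers everything short of a doubling in a composite of deaths and severe morbidity.

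**No-increase wording is common for a non-inferiority hypothesis.** True, and the article's Discussion speaks of non-inferiority. The wording alone would be a small matter; it counts because of the margin's size relative to the base rate.

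**The reader will see more than pass or fail.** Crude proportions, component analyses and independent review of each primary event are planned. These help, but they do not put the upper limit of the risk difference in front of the reader.

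Four stronger readings are tempting, and the documents do not support them:

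- A reader might infer that the abstract contradicts the rule. It says only that the service "is expected to be equally safe and more comfortable and convenient for the women, with lower economic costs", which is an expectation and not a criterion for the conclusion.
- A reader might infer that a rise as large as the margin would usually pass. It would not: a true 20% against 10% passes 5.5% of the time, and a true 15% against 5% about 6%.
- A reader might infer that the margin is bound to become more permissive. The base rate could equally prove higher, and then the chance of passing with no effect falls to about 65%.
- A reader might conclude that a low hospital rate should make the result inconclusive unless a relative doubling is also excluded. With 125 per group and a true 5% in both groups, that extra test would be met only about 11% of the time given six or fewer hospital events (log risk ratio, one-sided 95%). That is a debatable trade-off, and the plan is not defective for omitting it.

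**Conclusion.** The concern holds as a limit on what the primary result can be said to show. Meeting the margin excludes an absolute increase of more than 10 percentage points in the composite, equivalent to a doubling if the hospital rate is 10%. It does not establish that the risk is not increased: at that rate, a true relative rise of 30% passes about 55% of the time and one of 50% about 34%.

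The figures assume 125 analysed women per group, an unadjusted comparison and a one-sided 95% Wald limit; Newcombe limits lower them by at most a few points, with the largest drop (47% to 41%) in the doubling from 5%. The results at 5% and 18.8% are illustrations. The 4.4% to 18.8% interval rests on an inferred 8 events in 80 women. The documents do not split the 10% by component, so nothing can be said about how much of any rise would be deaths.

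**What to change.** Keep the margin and the sample size, and make two changes before analysis.

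1. **Wording of the primary conclusion.** If the rule is met, state that an absolute increase of more than 10 percentage points in the composite is excluded. Add that this does not establish equal safety or the absence of an increased risk. Align the hypothesis sentence in the Introduction with this.
2. **Reporting.** Beside the planned odds ratio, report the risk difference, both crude and standardised from the planned logistic model, with its upper one-sided 95% limit. Give that limit in percentage points and relative to the observed hospital-group rate, so that the reader sees how large an increase remains compatible with the data whatever the base rate turns out to be.

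The cost is a more modest safety claim, edits to the hypothesis, sample-size and analysis sections, and one additional estimate from a model already planned. No extra women are needed. For comparison, a 5-point margin under the same assumptions would require 446 women per group (892 in total), which is why the remedy lies in the claim and its reporting.

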### Data analysis

After inclusion in the study, baseline data such as patient demographics, medical and obstetric history, and pregnancy data will be collected and registered in a case report form before entering and coding the data in a study-specific electronic record. After delivery, the remaining relevant data for the assessment of maternal mortality and morbidity and perinatal outcomes will be collected from the hospital's electronic patient journal and registered in the study-specific HOME records. All primary and secondary outcome data will be registered, in addition to gestational age at birth and birthweight (Table 2).

The composite primary outcome will be analyzed using logistic regression analyses. Parity and gestational age will be included as potential confounding variables. Further, each component of the composite primary outcome and all secondary outcomes will be analyzed to provide further insight into the research question. The results will be presented as odds ratios with 95% confidence intervals, in addition to crude proportions (not adjusting for parity and gestational age).

The obstetric experts in the DAG will independently evaluate all composite primary outcomes continuously throughout the project period and without interference from anyone in the project group. The DAG will conclude whether any primary (severe adverse) outcomes are related to the study or not, and the results will be presented in detail in the study report.

The study participants' experience, mental wellbeing (depression and anxiety), sense of coherence, and self-efficacy will be described at the group level (hospital monitoring vs. home monitoring) at the two investigated time points (2–7 days after hospital admission or start of home monitoring and again at 10–12 weeks postpartum).

The cost-effectiveness of home monitoring compared to the hospital-monitored group will be described at the group level based on the estimated cost of each admission to different wards at Oslo University Hospital and outpatient visits from inclusion in the HOME study until delivery.

The generalizability of the study sample will be evaluated by comparing the study group characteristics with the general pregnant population, the entirety of the latter being registered due to the compulsory notification of each birth to the Medical Birth Registry of Norway (33). Only women with Norwegian language skills can participate, which excludes some groups, particularly a subgroup of newly immigrated women, limiting the generalizability of the study. The present study can, however, be considered a first step in providing more personalized and flexible follow-up for women with high-risk pregnancies. If the study results are reassuring, future projects may include more heterogeneous language and ethnic groups, thus testing home monitoring opportunities in more diverse pregnant populations.

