### Participant eligibility criteria

The patients eligible for participation in the study are ≥18 years old, Norwegian-speaking, singleton pregnant women requiring intensified follow-up after at least one initial comprehensive hospital assessment. The following indications for surveillance may be relevant for home monitoring (Table 1): hypertensive disorders (chronic hypertension, gestational hypertension, and/or preeclampsia), pPROM, and previous adverse obstetric outcomes (e.g., fetal death, severe preeclampsia, preterm delivery, and/or fetal growth restriction). Exclusion criteria for home monitoring include a clinical imminent health risk to the mother and/or fetus, including (but not restricted to) non-reassuring CTG, blood pressure, infectious or clinical signs or symptoms, and/or more than 1 h travel to the hospital. Women with an expected delivery or induction of delivery within a short period will not be recruited [e.g., preeclampsia at term (≥37 weeks), prelabor rupture of membranes (PROM) ≥37 weeks, or pPROM with indication for rapid delivery (e.g., discolored amniotic fluid, suspicion of chorioamnionitis or other severe infections, or pathological CTG)]. Insufficient support at home and a lack of understanding of the relevant HOME study's technical devices (to be tested before departure from the hospital) are also exclusion criteria for being offered home monitoring.

**Table 1 T1:** Clinical definitions of the inclusion criteria for home monitoring of high-risk pregnancies.

	Inclusion criteria	Additional definitions
1	Hypertensive disorders of pregnancy	
-	✓ Chronic hypertension	✓ Hypertension (systolic blood pressure ≥140 mmHg and/or diastolic blood pressure ≥90 mmHg) identified before or during the first 20 weeks of the present pregnancy
	✓ Gestational hypertension	✓ New-onset hypertension (defined above) at ≥20 gestational weeks during the present pregnancy
	✓ Preeclampsia	✓ Gestational hypertension (defined above) in addition to new-onset proteinuria or at least one other maternal sign of organ dysfunction according to International Society for the Study of Hypertension in Pregnancy criteria from 2018 (4)
2	Preterm premature rupture of membranes	✓ Rupture of membranes at <37 gestational weeks ✓ No present uterine contractions ✓ Cephalic presentation

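### The primary analysis of a non-randomised comparison adjusts for parity and gestational age but not for surveillance indication, and does not say that gestational age is taken at inclusion

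*Protocol article*

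**What the plan says.** On the primary analysis, the Data analysis section of the protocol article says "The composite primary outcome will be analyzed using logistic regression analyses", followed by "Parity and gestational age will be included as potential confounding variables". Odds ratios are to be reported "in addition to crude proportions (not adjusting for parity and gestational age"), so the contrast between adjusted and crude results is defined by those two variables.

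The only gestational age that this section names explicitly is in the sentence on outcome data: "All primary and secondary outcome data will be registered, in addition to gestational age at birth and birthweight (Table 2"). The section also says that pregnancy data are collected at baseline, without listing them.

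The Sample size section sets the margin ("The non-inferiority margin was set to 10"%), acknowledges that the groups are not parallel, and responds to this as follows: "another 20 women will be recruited to adjust for potential confounding factors such as parity and gestational age".

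Participant eligibility criteria and Table 1 admit women for three kinds of indication ("The following indications for surveillance may be relevant for home monitoring (Table 1")). Under Recruitment procedure, a senior obstetrician applies these criteria with a checklist, so the indication is on record for every woman at entry. Study setting and the two group descriptions give the timing: hospital-monitored women from December 2022, home-monitored women from June 2024, and an unstated number of hospital-monitored women recruited in the later period.

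**The concern.** Without randomisation, the adjustment set carries the burden of making the groups comparable. Indication is the most visible prognostic factor in the protocol's own text. Several components of the composite in Table 2 belong mainly to one indication: eclampsia and HELLP/ELLP to hypertensive disorders, sepsis to ruptured membranes. The home programme itself gives each indication different symptom questions and tests. Recruitment was largely sequential, so nothing in the design keeps the indication mix the same in both groups, and the named covariates do not include the variable that would correct a difference.

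The second gap is the timing of gestational age. Measured at inclusion, it is a proper confounder. Measured at birth, it follows monitoring and the complications under study, so adjusting for it could remove part of the effect being estimated. The text does not exclude that use.

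At stake is a safety conclusion. A false declaration of non-inferiority and a missed true one are both possible, depending on how the mix differs.

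**Working it through.** **The plan's own figures.** The inputs from the Sample size section are 10% in both groups, margin 10 points, one-sided 5%, power 80%. With unpooled variance, n per group = (1.645 + 0.842)² × 2 × 0.10 × 0.90 / 0.10² = 111.3, rounded up to 112, or 224 in total. This reproduces. 224 + 6 + 20 = 250 also adds up. Expected events are 0.10 × 250 = 25.

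**What the 20 women buy.** Going from 230 to 250 offsets a variance inflation of 250/230 = 1.087, which is an R² between group and covariates of 1 − 230/250 = 0.08. By normal approximation, power goes from 81.1% at 115 per group to 83.9% at 125. This is a gain in precision. It does not change the size of any bias from a factor left out of the model.

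**Hypothetical effect of an indication imbalance.** The documents give neither risks nor mix by indication, so all of the following inputs are assumptions:

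- Risks: hypertensive 16%, pPROM 8%, previous adverse outcome 2%.
- Mix A: 50/20/30%. Risk = 0.50 × 16 + 0.20 × 8 + 0.30 × 2 = 10.2%.
- Mix B: 35/15/50%. Risk = 0.35 × 16 + 0.15 × 8 + 0.50 × 2 = 7.8%.
- Difference with no true effect: 10.2 − 7.8 = 2.4 points, about a quarter of the margin.

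The next table gives the chance of declaring non-inferiority (upper one-sided 95% Wald limit for the risk difference below 10 points; exact binomial; 125 per group). True harm adds 10 points to the home risk.

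| Scenario | Hospital vs home, true 10-point harm | False non-inferiority | Hospital vs home, no true effect | Power |
|---|---|---|---|---|
| Same mix | 10% vs 20% | 5.5% | 10% vs 10% | 84.5% |
| Hospital A, home B | 10.2% vs 17.8% | 14.6% | 10.2% vs 7.8% | not a fair gain: inflated by bias |
| Hospital B, home A | 7.8% vs 20.2% | 1.6% | 7.8% vs 10.2% | 68.8% |

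At 112 per group, the false non-inferiority rate in the first two rows is 5.3% and 13.5%.

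**Range.** Take a simpler two-level indication. Bias = difference in risk × difference in mix. Risks of 15% vs 5% or 20% vs 5%, with mix differences of 10 to 30 points, give biases from 0.10 × 0.10 = 1.0 point to 0.15 × 0.30 = 4.5 points. If the bias favours home monitoring, the nominal 5% error at a true 10-point harm becomes 7.8% (1 point), 11.8% (2), 17.2% (3) or 28.3% (4.5), by normal approximation at 125 per group. More women do not help: with a 3-point bias the error is 16.5% at 115 per group and 17.2% at 125.

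**Why recruitment period is not simply another covariate.** Suppose that all home women are late and a share s of hospital women is late. Then R² between group and period is (1 − s)/(1 + s), and the variance inflation is (1 + s)/(2s). This is 5.5 at s = 10%, 3.0 at 20%, 2.2 at 30% and 1.5 at 50%. At s = 0 period cannot be separated from group at all. The documents do not give s.

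**Room in the model.** Group, parity and gestational age make three parameters, about 25/3 ≈ 8 events each. Adding indication (two) and site (one) makes six, about 25/6 ≈ 4 events each.

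**The case against.** The strongest reply has four parts.

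1. *The list may not be closed.* The Sample size section introduces its factors as examples, the Data analysis section does not say that there are no others, and a fuller plan may exist. This stands as a caution. However, the Data analysis section names the two covariates and defines the crude result by the absence of those same two. That is a published choice rather than a detail left unsaid.

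2. *No imbalance is shown.* One eligibility checklist is used, allocation follows equipment availability, and later hospital-monitored women enter for reasons unrelated to eligibility. Parity and gestational age may also capture part of an indication difference, for which the example gives no credit. All of this stands, and it is why the figures are hypothetical.

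3. *A small model suits few events.* This is right for ordinary logistic regression. It argues for a different adjustment method, not for leaving indication out.

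4. *The 20 women are a sample allowance for adjustment.* This is a fair reading, and as such the allowance is reasonable.

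Stronger readings are tempting, but the text does not support them:

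- A reader might infer that gestational age at birth is the planned covariate. It is named only among the registered outcome data, and calling gestational age a confounder suggests a baseline value. The defect is an unstated time point.
- A reader might infer that the bias favours home monitoring, on the view that women with a previous adverse outcome are currently uncomplicated. Table 1 does not say so, these women need intensified follow-up, and they may be given questions from the other risk groups.
- A reader might call the absence of recruitment period from the model an error. Period is nearly collinear with group, so entering it would cost much of the precision.
- Site could be made to look like a major omission, but recruitment is primarily in Oslo and the second hospital adds only some patients.

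**Conclusion.** The point holds in this form: the stated adjustment set omits surveillance indication, a prognostic factor known at entry for every woman, and leaves the timing of gestational age open, in a comparison that relies on adjustment for its validity. The sample size arithmetic is correct and is not at issue.

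The size of the resulting bias cannot be derived from the documents. Under the assumed inputs it runs from 1.0 to 4.5 points, with 2.4 points in the worked example, against a 10-point margin. The direction is unknown: the same imbalance either nearly triples the false non-inferiority rate (5.5% to 14.6%) or cuts power by about 16 points (84.5% to 68.8%). If the indication mix turns out equal, there is no bias from this source, but adjusting for indication is still the sound plan to fix before the comparison is made.

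**What to change.** 1. Add indication (three levels) to the adjustment set for the primary outcome, and state that gestational age is at inclusion, not at birth. Site may be added if numbers allow.
2. Because only about 25 events are expected, make the adjustment through a propensity score for group (about 125 women per group), standardisation or a penalised model, rather than a larger ordinary logistic regression. Standardisation or weighting also yields an adjusted risk difference on the scale of the margin.
3. Pre-specify a sensitivity analysis restricted to women recruited from June 2024. State that it will be imprecise, since the number of concurrent hospital-monitored women is not given. Do not enter recruitment period as a simple covariate.
4. Describe the 20 extra women as a precision allowance for covariate adjustment, which does not reduce bias from factors left out of the model.

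The cost is a change of analysis wording. Indication is on the entry checklist, and gestational age at inclusion should be available from the baseline pregnancy data. The statistical price is a slightly wider interval for the adjusted comparison.
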